**Fig 5 pone.0256278.g005:**
[figure not shown]
Partition of aorta sample to four quadrants.

**Fig 6 pone.0256278.g006:**
[figure not shown]
Section of aorta sample with square shape (size: 15 mm * 15 mm). One specimen by quadrant.

Young’s modulus (E) is a measure of the ability of a material to withstand changes in length (strain) when under lengthwise tension or compression (tensile stress). Maximum elastic modulus calculation was previously described by Duprey et al [20].

Briefly, we assume that the aortic wall is an incompressible material. Stress *σ* is defined by Eq (3):
$$Tensile\;Stress\left(\sigma (\varepsilon )\right)(Pa)=\frac{F}{A}$$(3)
F is the load and A the cross sectional area in mm². Strain is defined by Eq (4):
$$Strain(\varepsilon )=\frac{\Delta L}{L}$$(4)
ΔL represents the instantaneous stretch and L represents the length of the specimen. Sometimes referred to as the modulus of elasticity, Young’s modulus is directly related to the longitudinal stress divided by the local strain (local relative displacement) and can be derived using Eq (5):
$$Young^{\prime }s\;modulus(E)(Pa)=\frac{Tensile\;Stress\;(\sigma (\varepsilon ))}{Strain\;(\varepsilon )}$$(5)
The maximum elastic modulus from each sample will be taken from each curve as the slope of the tangent of the stress-strain relationship (Fig 7).

**Fig 7 pone.0256278.g007:**
[figure not shown]
The stress-strain relationship.

### Statistical analysis

The analyzed variables are continuous variables that will be expressed by their mean and standard deviation. We will test the normality of the variables with the Skewness and Kurtosis tests. STATA 14 statistical software (StataCorp, LP, College Station, Texas, and United States) will be used for the analyses. Continuous data will be analysed using a paired t-test or Wilcoxon test when variables will not follow a normal distribution. To study the correlation between MRI measurements and laboratory tests, we will use the parametric tests of correlation. In the absence of normality, we will use Spearman’s nonparametric test. Then we will use a univariate and multivariate linear regression model with the dependent variable being the MRI measurement. With a sample size of 100 patients, for an hypothesis H_0_: ρ = 0.4 and an hypothesis H_1_: ρ = 0.6, the statistical power is 0.84.

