**Fig 1 pone.0256278.g001:**
[figure not shown]
Flow chart of the study design.

Statistical analysis will be performed to establish whether there is a correlation between MRI compliance measures and laboratory aortic elasticity tests.

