## Discussion

Preliminary study about the aortic compliance evaluation from MRI in pre- and post-operative ascending aortic replacement surgery shown that the aortic root replacement by graft was not associated with changes in elastic properties of the descending aorta at short term [22], However, for the ascending aorta, we found on a short sample that a local variability could happen in the aortic stiffness between different quadrants [23].

In case of positive correlation between compliance and/or PWV of the aorta measured by cardiac-MRI and elasticity testing, it would demonstrate the robustness of cardiac MRI for the assessment of the elastic properties of the aorta, even if the compliance is a local parameter that only accounts for in-plane area change at a specific localization. It will be then be necessary to determine the risk thresholds for aortic wall rupture, which is responsible for aortic dissections. This could be used to monitor aneurysms of the ascending aorta or patients without dilatation but with a family member with an aneurysm or aortic dissection. Although the experiments will be performed under different settings (parameters obtained in-vivo from MRI versus ex-vivo evaluation for elastic testing), the results could conclude that cardiac MRI could also guide surgical indications for replacement of the ascending aorta based on patient-specific biomechanical criteria rather than absolute diameter measurements that do not consider the specific characteristics of each patient’s artery walls. The potential heterogeneity of the cohort could be a limitation but the size of the considered cohort should reduce this bias.

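### The quoted power of 0.84 belongs to a test against ρ = 0.4, but the planned correlation tests and the robustness conclusion are not tied to that null and read most naturally as tests of zero

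*Protocol article*

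**What the plan says.** Three places in the protocol article bear on the point.

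- **Sizing (Statistical analysis, last sentence).** "With a sample size of 100 patients", the hypotheses are "for an hypothesis H_0_: ρ = 0.4" and "an hypothesis H_1_: ρ = 0.6", and "the statistical power is 0.84". Neither alpha nor sidedness is given.
- **Analysis (same section).** "To study the correlation between MRI measurements and laboratory tests, we will use the parametric tests of correlation". Spearman's test replaces it if normality fails, and linear regression follows. No comparison with 0.4, confidence-limit rule or minimum r is mentioned.
- **Question and conclusion.** After the Fig 1 caption in Materials and methods: "Statistical analysis will be performed to establish whether there is a correlation between MRI compliance measures and laboratory aortic elasticity tests". The Discussion says of a positive correlation, with no minimum size, that "it would demonstrate the robustness of cardiac MRI for the assessment of the elastic properties of the aorta".

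**The concern.** Setting the null at 0.4 says, in effect, that a correlation of 0.4 or less between MRI and bench testing is not good enough. That is a sensible position when an imaging measure is compared with a laboratory reference, because the strength of the association decides whether the measure is useful. The analysis paragraph does not carry this standard forward. As usually run, the Pearson and Spearman tests have a null of zero, and a question about the existence of a correlation points the same way.

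If the tests are run in that usual form, the quoted power describes a different test. A correlation that the sizing sentence treats as null would then nearly always come out significant and could be read, under the Discussion's wording, as support for the robustness of cardiac MRI.

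**Working it through.** **Inputs.** From the Statistical analysis section: N = 100, ρ0 = 0.4, ρ1 = 0.6, power 0.84. Assumed, because not stated: alpha 0.05, computed one-sided and two-sided. The null of the analysis test is also not stated; zero is inferred.

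**Step 1: reproduce the plan's figure.** Fisher z against 0.4:

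power = Φ[(atanh 0.6 − atanh 0.4) × √(N − 3) − z]

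atanh 0.6 = 0.6931, atanh 0.4 = 0.4236, √97 = 9.849, so the first term is 0.2695 × 9.849 = 2.654.

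- One-sided 0.05: Φ(2.654 − 1.645) = Φ(1.009) = 0.844. This matches 0.84.
- Two-sided 0.05: Φ(2.654 − 1.960) = Φ(0.694) = 0.756. This does not match.

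The small-sample bias term changes these only to 0.846 and 0.759. The arithmetic behind 0.84 is therefore sound, and the figure belongs to a one-sided test of 0.4.

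**Step 2: does 0.84 describe a test of zero?** At ρ = 0.6, two-sided 0.05, the power is Φ(0.6931 × 9.849 − 1.960) = Φ(4.87), which exceeds 0.999. A power of 0.84 for that test would need only [(1.960 + 0.994)/0.6931]² + 3 = 21.2, that is 22 patients. It does not.

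**Step 3: significance thresholds at N = 100.**

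| Test | One-sided 0.05 | Two-sided 0.05 |
|---|---|---|
| ρ0 = 0: t/√(98 + t²) | r = 0.165 | \|r\| = 0.197 |
| ρ0 = 0.4: tanh(0.4236 + z/9.849) | r = 0.530 | r = 0.553 |

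The gap is large on either convention. An observed r of 0.197 corresponds to 0.197² = about 4% shared variance. For r = 0.20 the 95% CI is tanh(0.2027 ± 1.960/9.849), or about 0.004 to 0.38. The result is significant against zero, yet its whole interval lies below the sizing null.

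**Step 4: how often each test is significant when the true ρ is 0.4.**

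- Zero test, two-sided 0.05: Φ(0.4236 × 9.849 − 1.960) = Φ(2.21) = 0.987.
- One-sided 0.05 test against 0.4: 5% by construction (2.5% in the upper direction for a two-sided 0.05 test).

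A simulation with 100,000 replicates gave 0.987, 0.052 and 0.026. At a true ρ of 0.3 the zero test is significant with probability Φ(0.3095 × 9.849 − 1.960) = 0.862.

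**Step 5: power of the possible remedies at ρ = 0.6.** For Spearman, inflate the variance by 1.06, so √(97/1.06) = 9.566 and the first term is 0.2695 × 9.566 = 2.578.

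| Rule against 0.4 | Pearson | Spearman |
|---|---|---|
| One-sided 0.05 (90% CI limit) | 0.84 | Φ(2.578 − 1.645) = 0.82 |
| Two-sided 0.05 (95% CI limit) | 0.76 | Φ(2.578 − 1.960) = 0.73 |

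**The case against.** The article does not write down a null of zero for the analysis. The only null it states is 0.4, in the same paragraph, and a Fisher z test against 0.4 is also a parametric test of correlation. An analysis plan that is not shown may name it. A reader might therefore go too far in concluding that 0.4 will definitely never be tested; the text neither says so nor excludes such a test.

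A reader might also infer a formal rule under which r of about 0.20 is declared a success. The documents contain no success criterion. The Discussion sentence is conditional prose, and the same paragraph says that risk thresholds would still have to be determined.

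Nor is the study underpowered or the analysis invalid if the zero test is what is run. Its power at ρ = 0.6 exceeds 0.999, and a reported r of 0.20 would be visibly weak.

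These points limit the severity and the certainty. They do not remove the conflict, which lies between things the article states rather than in what it omits. It gives a null for sizing, tests in their standard form, a question about existence, and a conclusion with no minimum size. Nothing links the first to the other three.

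**Conclusion.** The point holds as a mismatch between the power statement on one side and the analysis and conclusion on the other. It should be fixed but does not threaten the study's validity. The 0.84 is correctly calculated, but only for a one-sided 0.05 Fisher z test against 0.4.

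On the most natural reading, the planned test has a much lower bar: |r| = 0.197 instead of about 0.530. It would also be significant about 98.7% of the time at the very correlation used as the sizing null. The practical risk is over-interpretation of a weak association.

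The size rests on two assumptions: that the analysis tests zero, and that it uses two-sided 0.05. At one-sided 0.05 the zero-test threshold falls to 0.165 and the gap widens.

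**What to change.** **Preferred.** State the primary test as Fisher's z against |ρ0| = 0.4, in the expected direction for each MRI measure, at one-sided 0.05. Equivalently, the 90% CI limit nearer zero must lie beyond 0.4, which for Pearson means |r| above about 0.530. Power stays at 0.84, or about 0.82 for Spearman with the 1.06 variance factor. Tie the Discussion's robustness conclusion to this rule and report the test against zero as secondary.

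**If a two-sided 95% CI is wanted** (|r| above about 0.553), restate the power as about 0.76, or about 0.73 for Spearman. Keeping 0.84 beside that rule would create a new mismatch.

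**If a test of zero is really intended**, say so with its alpha and sidedness, restate the power for that test, and do not claim robustness from significance alone.

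The cost is a few sentences and one further line of analysis code, with no new data. Under the first two options a positive conclusion becomes harder to reach, as the sizing hypothesis implies it should be.

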## Discussion

Preliminary study about the aortic compliance evaluation from MRI in pre- and post-operative ascending aortic replacement surgery shown that the aortic root replacement by graft was not associated with changes in elastic properties of the descending aorta at short term [22], However, for the ascending aorta, we found on a short sample that a local variability could happen in the aortic stiffness between different quadrants [23].

In case of positive correlation between compliance and/or PWV of the aorta measured by cardiac-MRI and elasticity testing, it would demonstrate the robustness of cardiac MRI for the assessment of the elastic properties of the aorta, even if the compliance is a local parameter that only accounts for in-plane area change at a specific localization. It will be then be necessary to determine the risk thresholds for aortic wall rupture, which is responsible for aortic dissections. This could be used to monitor aneurysms of the ascending aorta or patients without dilatation but with a family member with an aneurysm or aortic dissection. Although the experiments will be performed under different settings (parameters obtained in-vivo from MRI versus ex-vivo evaluation for elastic testing), the results could conclude that cardiac MRI could also guide surgical indications for replacement of the ascending aorta based on patient-specific biomechanical criteria rather than absolute diameter measurements that do not consider the specific characteristics of each patient’s artery walls. The potential heterogeneity of the cohort could be a limitation but the size of the considered cohort should reduce this bias.
